#### 2.5.4 Primary and Secondary Outcomes

The primary outcome for the effectiveness trial will be child lifestyle pattern score ‘Discretionary food and screen time’ at 18 months. This is a composite measure of child diet, physical activity and screen time derived from a previous analysis (44) of the INFANT RCT (13) and INFANT Extend RCT (33) using principal component analysis. This has been selected as the primary outcome based on previous research (44) confirming the early clustering of these behaviours into unhealthy versus healthy lifestyle patterns in children as young as 18 months of age. Further, these lifestyle patterns track from early childhood into later childhood and adulthood, and are associated with overweight and obesity (45).

Secondary outcomes of the effectiveness trial will include (i) proportion of mothers with any breastfeeding at 12 months; (ii) energy-balance behaviours including child diet (fruit, vegetables, non-core drinks and snacks), child time physically active and sedentary, scores on the ‘Fruit, vegetables and outdoor time’ lifestyle pattern (12 & 18 months), and scores on the ‘Discretionary food and screen time’ lifestyle pattern (12 months) (44); (iii) infant BMIz at 12 months and 18 months, and (iv) child classification as overweight or obese according to WHO definitions (46).

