#### 2.5.5 Sample Size

The trial aims to recruit 1,500 primary carer/infant dyads in each arm (total 3,000). Assuming a conservative attrition rate of 33%, it is expected that complete data on 2,000 primary carer/infant dyads (1,000/arm) will be collected. The statistical software PASS version 14.0.9 (NCSS, LLC) was used for all power calculations, assuming that 190 first-time parent groups will run in each arm with an average number of 5.4 children with complete data per group and a coefficient of variability in group size of 0.32, as observed in the INFANT RCT (13) (α=0.05; two-sided tests). A target sample size of 1,000 infants per arm achieves 80% power to detect a mean difference between arms of at least 0.17 points in the lifestyle score ‘Discretionary food and screen time’ at 18 months [primary outcome; standard deviation within clusters (SD) =1.21, intracluster correlation coefficient (ICC) = 0.048]. In our former INFANT trial (44) the difference in “Discretionary food and screen time” pattern score was 0.29 (95% CI: 0.08, 0.49).

The target sample size (1,000 infants per arm) also achieves 80% power to detect the following differences in secondary outcomes:

1) 6.2% increase in the proportion of mothers with any breastfeeding at 12 months assuming the proportion in the control group will be 27% (ICC =0.05);2) a mean difference (at 18m) between study arms of a) 0.24 serve/day in fruit [SD=1.7, ICC=0.071]; b) 0.25 serve/day in vegetables [SD=2.0, ICC=0.000]; c) 0.06 serve/day in non-core drinks [SD=0.44, ICC=0.034]; d) 0.06 serve/day in non-core sweet [SD=0.39, ICC=0.064]; e) 0.05 serve/day in non-core savoury [SD=0.33, ICC=0.047]; f) 6.7 min/day of screen use [SD=44, ICC=0.11]; and g) 18.4 min/day of physical activity [SD=143, ICC=0.018]. While individual energy-balance behaviour changes appear small, modest increments in energy consumption (126-189kJ/day (30-45 calories)) are estimated to promote population weight gain over time. Collectively these changes have capacity to influence weight gain trajectories at a population level (47, 48);3) a mean difference between arms of at least 0.13 change in BMIz score by 12 months [SD=1.0, ICC= 0.021]. Assuming a mean BMIz of 0.41, a 0.13 reduction in BMIz to 0.28 equates to a 1.3% reduction in prevalence of overweight and obesity, considered meaningful at a population level.

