#### 2.5.6 Data Collection and Analysis

Infant diets will be measured by a validated Food Frequency questionnaire (FFQ) with average percentage categorical agreement against three days of 24 hour recall of 62-64% (49). Infant physical activity will be measured using a single parent-reported question with good test-retest reliability (ICC 0.62) (50). Infant screen time will be measured using a single parent-reported question with excellent reliability (ICC 0.84) (51). Change in BMIz measured at 12 and 18 months will be derived from child height and weight which is routinely collected by MCH nurses and will be made available in de-identified form to the research team. These data are typically available for 80% and 71% of infants at 12 and 18 months respectively (52). Lifestyle pattern scores will be calculated as linear combinations of the standardized dietary (fruit, vegetables, water, discretionary sweet foods, discretionary savory foods), outdoor and television viewing items, using the principal component analysis factor loadings previously published from the combined INFANT and INFANT Extend datasets (44).

Covariates will include self-reported parent socio-demographic characteristics (including marital status, education level, age, sex, Indigenous status, language spoken at home, country of birth, years lived in Australia, health care card holder) parent weight and height, pre-pregnancy weight, self-rated coping, sleep and health, infant sex, birth weight and temperament. Baseline characteristics will be compared between arms using linear mixed models (LMM) or generalized estimating equations (GEE) with link and distribution selected based on the type of variable. The effect of the intervention on the primary outcome (‘Discretionary food and screen time’ lifestyle pattern) will be estimated using a LMM including arm, time (12 and 18 months), interaction arm-time and any baseline variable showing clear imbalance between arms (covariates) as fixed effects. The same LMM model will be used for numerical secondary outcomes. All mixed models will include MCH group as a random effect to account for clustering. The effect of the intervention on proportion of mothers with any breastfeeding at 12 months will be estimated using a GEE model with logit link and binary distribution including arm, time (12 and 18 months), interaction arm-time and baseline confounders. If appropriate, multiple imputation will be used to handle missing data.

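### The primary mixed model uses two scores per child but names only MCH group as a source of dependence; fitted as written it costs some power and weakens protection against dropout

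*Protocol article*

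**What the plan says.** All references are to the protocol article.

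- Section 2.5.4 sets the endpoint at one time point: "The primary outcome for the effectiveness trial will be child lifestyle pattern score ‘Discretionary food and screen time’ at 18 months".
- Section 2.5.6 analyses it with both follow-up times in one model. The effect "will be estimated using a LMM including arm, time (12 and 18 months), interaction arm-time and any baseline variable showing clear imbalance between arms". Numerical secondary outcomes get the same model.
- The one statement on dependence, also in section 2.5.6, is "All mixed models will include MCH group as a random effect to account for clustering".
- On missing data, section 2.5.6 says "If appropriate, multiple imputation will be used to handle missing data".
- Section 2.5.5 sizes the trial for the 18-month score alone. With 1,000 infants per arm it "achieves 80% power to detect a mean difference between arms of at least 0.17 points in the lifestyle score", using "standard deviation within clusters (SD) =1.21, intracluster correlation coefficient (ICC) = 0.048" and "α=0.05; two-sided tests". It assumes 190 groups per arm, 5.4 children with complete data per group, a coefficient of variation of group size of 0.32, and 33% attrition from 1,500 per arm.

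**The concern.** A child measured at 12 and at 18 months gives two correlated scores. With a group effect alone, the model treats these as no more alike than scores from two different children in the same parent group. Two things follow.

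First, part of the child-level variance is attributed to the group. That inflates the standard error of a between-arm contrast at one time. It also denies the arm-time interaction the gain from each child serving as their own control.

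Second, a child's 12-month score does not specifically inform that child's missing 18-month score. The usual benefit of a likelihood-based repeated-measures model, validity when loss depends on observed earlier scores, is then largely lost. At stake are the power of the primary comparison and, under some patterns of loss, its bias. The model also serves the numerical secondary outcomes, so the same gap carries over to them.

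**Working it through.** **Inputs from section 2.5.5:** k = 190 groups per arm, m = 5.4, CV = 0.32, within-cluster SD 1.21, ICC 0.048, difference 0.17, two-sided α = 0.05. **Assumed:** within-child correlation ρ (within group) of 0.3, 0.5 or 0.7, since the documents give none.

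**Step 1, the plan's own figure.**
- Within-group variance: 1.21² = 1.4641.
- Group variance: 1.4641 × 0.048/0.952 = 0.0738.
- Total: 1.5379 (SD 1.24).
- Design effect: 1 + ((1 + 0.32²) × 5.4 − 1) × 0.048 = 1.238.
- Children per arm: 190 × 5.4 = 1,026.
- SE = √(2 × 1.5379 × 1.238/1,026) = 0.0609.
- Power = Φ(0.17/0.0609 − 1.96) = 0.797.

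Taking 1.21 as the total SD with n = 1,000 gives 0.806. The stated 80% reproduces. It concerns a single measurement and is not affected by this point.

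**Step 2, what the group-only model estimates (complete data, equal groups).** Equating mean squares, a variance of ρ × 1.4641/(2m − 1), with 2m − 1 = 9.8, moves from the residual to the group component.

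- 18-month SE ratio: √[(group* + residual*/m)/(0.0738 + 1.4641/m)], where the denominator is 0.3449.
- Interaction SE ratio: √[residual*/(1.4641 × (1 − ρ))].
- Power: Φ[(0.17 − 1.96 × ratio × 0.0609)/0.0609]. The estimate's true spread is unchanged; only its reported SE grows.

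| ρ | variance moved | group* | residual* | 18-month SE ratio | power at 0.17 | interaction SE ratio |
|---|---|---|---|---|---|---|
| 0.3 | 0.0448 | 0.1186 | 1.4193 | 1.05 | 0.77 | 1.18 |
| 0.5 | 0.0747 | 0.1485 | 1.3894 | 1.08 | 0.75 | 1.38 |
| 0.7 | 0.1046 | 0.1784 | 1.3595 | 1.12 | 0.73 | 1.76 |

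**Step 3, simulation with varying group sizes.** Two separate sets of REML fits agree in direction and roughly in size (values for ρ = 0.3/0.5/0.7).
- Power at 0.17: 78/78/75% in one set and 76/74/72% in the other.
- Interaction SE excess: 15/36/74% and 21/35/76%.
- 18-month SE excess: 4/8/11% in the first set; about 2-12% across runs of the second.
- Type I error of the 18-month contrast (second set): 0.048/0.036/0.029.

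**Step 4, loss at 18 months.** Simulated at ρ = 0.5 with about 33% loss overall and every child seen at 12 months. Simulation error on the bias is about 0.003-0.005.

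| Loss mechanism (assumed) | bias, group only | bias, child term added |
|---|---|---|
| Completely random | −0.003 | −0.004 |
| Depends on 12-month score, same in both arms | 0.002 | 0.001 |
| Depends on 12-month score in the intervention arm only (logit slope 0.5 per SD) | −0.086 | 0.003 |
| Same dependence, retention 75% vs 60% | 0.040 | 0.000 |

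In the last two rows the group-only test rejects a true null in 24% and 10% of runs. Multiple imputation from the 12-month score, separately by arm, brings those two biases to −0.001 and 0.005.

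**The case against.** A reader might infer that the plan makes MCH group the sole covariance term. The documents do not support that. The sentence says models will include a group effect; it does not exclude other terms. A within-child residual covariance is not a random effect, so it is compatible with the sentence. A condensed article may leave that detail to a fuller plan. This stands as a limit on the claim. What remains is that the article writes out the primary model term by term and, on dependence, names the group and omits what is likely the strongest correlation in the data.

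A reader might also infer that dropout biases the primary result. The documents do not support that either. Bias needs loss that depends on the 12-month score and differs between arms, with no adequate imputation. Sections 2.5.1 and 2.5.3 plan the same recruitment, follow-up and assessment strategies in both arms, call 33% attrition conservative (section 2.5.5), and cite 85% retention in the original trial. Different loss is plausible, because the arms are non-randomised and recruited one after the other (6 months against two years), but it is not shown. The imputation provision could remove the bias. It is conditional and names no model, and it would not correct the standard error while the analysis model lacks a child term.

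Finally, the largest error is in the interaction, which is neither the primary effect nor what the trial is powered for.

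**Conclusion.** The point holds in limited form, at moderate severity. The covariance structure, taken at face value, is misspecified for two scores per child. For the primary contrast with complete data the consequence is modest and conservative: a standard error about 2-12% too large and power of roughly 72-78% instead of 80%. It creates no risk of false positives there, and the sample-size calculation itself is sound. The arm-time standard error is about 15-76% too large.

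Bias of the 18-month contrast ranges from about zero to about half of the 0.17 target (0.086/0.17 = 0.51), depending entirely on how loss arises and whether imputation uses the 12-month score by arm. All sizes rest on an assumed within-child correlation of 0.3-0.7, and the bias figures also on assumed loss mechanisms. Calling this a must-fix error, or saying that the primary result will be biased, would go beyond the documents.

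**What to change.** Replace the sentence on clustering in section 2.5.6 with wording such as: mixed models with two time points will include random effects for MCH group and for child within group (or an unstructured within-child residual covariance); the primary effect is the arm contrast at 18 months from this model, using all children with a 12- or 18-month score.

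If multiple imputation is used, state that the imputation model includes the 12-month score and is fitted separately by arm, and keep the child term in the analysis model.

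The cost is one or two sentences and one extra model term, with no new data and no change to the sample size. If the analysts already intend a within-child term, the edit only makes that explicit.

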##### 2.4.4.2 Fidelity and Adaptation

It is anticipated that contextual modifications will occur, therefore fidelity and adaptation data will be explored using FRAME (39) (Framework for Reporting Adaptations and Modifications-Enhanced) to understand the rationale for modification and impacts on fidelity and/or effectiveness. Questions will be embedded into the 12-months post-training online survey to assess changes to planned INFANT implementation, and the types and context of adaptations made. Qualitative interviews will be conducted with a purposeful sample of these staff (with high/low fidelity, high/low barriers) to explore key factors influencing implementation, and adaptations made to implementation strategies. This will enable the fit of the intervention and implementation strategies to be documented and reviewed (40).

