### 2.5 Effectiveness Trial

#### 2.5.1 Trial Design

An embedded non-randomised controlled trial will assess the effectiveness and cost-effectiveness of INFANT when delivered at scale. The trial will involve comparing primary and secondary effectiveness outcomes between a group of INFANT participants (intervention arm) and a non-randomised comparison group recruited within the same communities prior to the implementation of INFANT (usual care arm). This approach enables comparison of outcomes between parents and infants exposed and not exposed to the intervention living in the same geographical areas and therefore sharing socio-demographic characteristics and having access to the same health services. The risk of bias will be reduced by replicating strategies for recruitment, follow-up and assessment in both trial arms and adjusting for unbalanced baseline characteristics. This trial design was deemed appropriate for assessing the effect of INFANT when implemented at scale in real-world conditions, enabling natural dissemination and uptake to be captured. A cluster randomized design with communities allocated to intervention or usual care was deemed not feasible because the prospect of being randomised to the control arm is likely to reduce participation. Within communities, the prospect of parent groups being randomised to a control arm is unethical (given the known efficacy of the intervention) and contamination between groups would be unavoidable. A stepped-wedge cluster randomised study design (43) was also considered but ruled out as randomisation of LGAs to an implementation time period may interfere with natural uptake under real world conditions.

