#### 2.5.3 Study Procedures

Families will be recruited over a 6-month period for the comparison arm and over a two-year period for the intervention group (**Table 1**). The comparison (usual care) group will be recruited prior to the implementation of INFANT by health services who have expressed interest prior to undergoing INFANT training. If sample size is not achieved from these LGAs, recruitment will be extended to other LGAs ensuring a mix of metro, regional, rural LGAs and various levels of socioeconomic disadvantage. There will be a three-month gap between recruitment of the last comparison participant and the commencement of recruitment for INFANT implementation participants. This gap ensures comparison participant infants will be too old to enroll in INFANT sessions and thus reduce potential for contamination.

Eligible parents will be invited to participate *via* SMS (with up to 2 reminders) sent by participating organisations. The SMS will contain a link to an online screening and consent process with consenting parents invited to complete online surveys when infants are aged ≤ 3 months (T1), 12 months (T2) and 18 months (T3) (**Table 1**). Up to three reminders will be generated for non-responders to follow up survey invitations. Strategies will be employed to promote retention (e.g. personalised newsletters, reimbursement for time spent completing surveys) which have been used successfully in the original INFANT trial, which achieved 85% retention over two years across both study arms (13).

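### INFANT is adopted by health service and period, but the model and the power calculation cluster only on parent group, so the standard error omits service-level variation and may be wrong in either direction

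*Protocol article*

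**What the plan says.** Section 2.5.6 gives the primary model as a linear mixed model with arm, time, their interaction and clearly imbalanced baseline variables as fixed effects. On clustering it says: "All mixed models will include MCH group as a random effect to account for clustering". No service or LGA term is named, and the listed covariates are parent and infant characteristics.

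Section 2.5.5 uses the same unit for power, "assuming that 190 first-time parent groups will run in each arm", with 5.4 children per group on average and an ICC of 0.048. The term MCH group is not defined. However, 190 groups per arm against 79 LGAs in the state shows that the power calculation counts parent groups, not services.

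Exposure is set at a higher level. Under sections 2.4.1 and 2.4.2 a health service signs up, has staff trained and then delivers. The comparison families are "recruited within the same communities prior to the implementation of INFANT" (section 2.5.1), and section 2.5.3 describes them as "recruited prior to the implementation of INFANT by health services who have expressed interest prior to undergoing INFANT training". The same section adds: "If sample size is not achieved from these LGAs, recruitment will be extended to other LGAs". On delivery, section 2.4.4.2 says: "It is anticipated that contextual modifications will occur".

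**The concern.** Parent groups in one service and one period have in common that service's decision to adopt, its implementation plan and whatever else happened locally in that period. If INFANT works better in some services than in others, or if local conditions shift between the two recruitment windows, the 190 groups in an arm are not 190 independent pieces of information about the arm difference. The stated aim is effectiveness at scale, so services are the population to which the result is to be carried.

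Recruiting both arms in the same communities removes stable differences between services from the arm comparison. It does not remove a service-by-period or service-by-arm component. If comparison recruitment moves to other LGAs, even the stable differences no longer fully cancel. At stake are the coverage of the confidence interval for the primary outcome and the meaning of the 80% power.

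**Working it through.** **Inputs from section 2.5.5:** within-cluster SD 1.21; ICC 0.048; 190 groups of 5.4 per arm; target difference 0.17; two-sided 5%.

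**The plan's own figure**
- Total variance = 1.21²/(1 − 0.048) = 1.538. Between-group part g² = 0.048 × 1.538 = 0.0738. Within-group part e² = 1.464.
- Variance of a group mean: b = 0.0738 + 1.464/5.4 = 0.345.
- SE = √(2 × 0.345/190) = 0.0603. Power = Φ(0.17/0.0603 − 1.96) = 80.5%.
- Allowing for the stated coefficient of variation of group size, 0.32 (design effect 1.232), gives SE 0.0608 and power 79.9%. The 80% reproduces with parent groups as the independent units.

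**Adding a service-by-period component (assumed)**

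Let s² = ρ × 1.538, independent between services and periods, with J equal-sized services supplying both arms. The equal-group form is used.
- SE reported by the parent-group model ≈ √(2(s² + b)/190)
- True SE = √(2(s²/J + b/190))
- True two-sided error = 2(1 − Φ(1.96 × model SE/true SE)); power with a correct SE = Φ(0.17/true SE − 1.96)

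Example, ρ = 0.01 and J = 40: s² = 0.0154, model SE 0.0616, true SE 0.0663, error 6.9%, power 72.7%.

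| Services | Error, ρ = 0.01 | Power, ρ = 0.01 | Error, ρ = 0.02 | Power, ρ = 0.02 |
|---|---|---|---|---|
| 20 | 9.3% | 66% | 13.2% | 55% |
| 40 | 6.9% | 73% | 8.6% | 66% |
| 79 | 5.7% | 76% | 6.3% | 73% |

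At ρ = 0.005, 40 services give 6.0% and about 77%; 79 services give 5.4% and about 78%.

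**The opposite pull**

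Now assume also a stable service ICC of 0.02 (c² = 0.02 × 1.538 = 0.0308), the same services in both arms, and no service term in the model. The stable part cancels from the true SE but inflates the model SE to √(2(c² + s² + b)/190). At ρ = 0.01 the model SE is 0.0642 and the error becomes 8.0% (20 services), 5.8% (40), 5.1% (60) and 4.7% (79).

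**Variation in the intervention arm only**

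Here the true variance is s²/J + 2b/190. At ρ = 0.01, power is 73%, 76.5% and 78.5% with 20, 40 and 79 services.

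**Incomplete overlap**

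A simulation (2,000 runs per scenario) with 15 services, half of them not shared between arms, a service SD of 0.13 to 0.19 and no variation in effect gave an error of 8% to 11%.

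**The case against.** Several stronger readings are tempting, and the documents do not support them.

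- **The intervals are certainly too narrow and the error rate is above 5%.** This is not established. With full overlap and a stable service ICC of 0.02 left out of the model, the error at 79 services is 4.7%. A simulation with 60 services, service SD 0.19 and effect SD 0.2 gave a true-to-model SE ratio of 1.00. The offset does not rescue 20 services (8.0%), and extension to other LGAs would weaken it.
- **All groups in a service share the same facilitators.** Section 2.4.2 sets one trained staff member as the minimum, so a service may have several.
- **Expected local adaptation proves an inflated false-positive rate.** Adaptation of INFANT exists only in the intervention arm. If INFANT had no effect in any service, adaptation could not create false positives; only local period shifts could, and the article gives no size for those. Expected adaptation bears on power and generalisability.
- **The 80% is wrong.** It reproduces under section 2.5.5's own assumptions.

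The assumed range also deserves scrutiny. An ICC of 0.01 in both arms implies an SD of the effect between services of √(2 × 0.0154) = 0.175; at 0.02 it is 0.248. Around a mean of 0.17, about 17% and 25% of services would then have an effect in the wrong direction. Smaller values are plausible.

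Finally, the article is condensed, and further nesting might be in an analysis plan that is not shown. That is fair for details such as the degrees-of-freedom method. But the article is not silent on clustering: it names one unit for all mixed models and powers on that unit.

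**Conclusion.** The point holds in a conditional form. INFANT is adopted by service, and arm follows service and period, while the stated model and the power calculation stop at the parent group. The standard error can therefore be wrong in either direction. It is too small if effects or period shifts differ between services, most of all with few services or with comparison families from other LGAs. It is slightly too large if the same services supply both arms and stable differences dominate.

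The size cannot be fixed from the article, because neither the number of contributing services nor any service-level variance is given. Over the assumed range the consequence runs from negligible, with most of the 79 LGAs, to material, with about 20 services. The discussion section itself says that uptake lies outside the research team's control, so a large number of services cannot be taken for granted. This is a change worth making, not an error in a stated figure.

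**What to change.** **Section 2.5.6.** Add to the mixed models a random intercept for health service (or LGA) and a random service-by-arm effect, with parent group nested within service and a small-sample degrees-of-freedom correction. Cluster the breastfeeding GEE by service, with a small-sample-corrected variance. Using both service terms deals with the error in either direction.

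**Section 2.5.5.** State that the 80% assumes no variation between services in effect or period shift. Give power over a range of service numbers and service-by-period ICCs, for example 0.005 to 0.02.

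**Cost.** Wording and a more cautious power statement. No new sample is needed, and service should be recordable for each family because participating organisations send the invitations. The downside is wider intervals if services do differ.
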